## Abstract

**Introduction:**

Descendants of patients with dementia have a higher risk to develop dementia. This study aims to investigate the uptake and effectiveness of an online tailor-made lifestyle programme for dementia risk reduction (DRR) among middle-aged descendants of people with recently diagnosed late-onset dementia.

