**Methods and analysis:**

Demin is a cluster randomised controlled trial, aiming to include 21 memory clinics of which 13 will be randomly allocated to the passive (poster and flyer in a waiting room) and 8 to the active recruitment strategy (additional personal invitation by members of the team of the memory clinic). We aim to recruit 378 participants (40–60 years) with a parent who is recently diagnosed with Alzheimer’s disease or vascular dementia at one of the participating memory clinics. All participants receive a dementia risk assessment (online questionnaire, physical examination and blood sample) and subsequently an online tailor-made lifestyle advice regarding protective (Mediterranean diet, low/moderate alcohol consumption and high cognitive activity) and risk factors (physical inactivity, smoking, loneliness, cardiovascular diseases (CVD), hypertension, high cholesterol, diabetes, obesity, renal dysfunction and depression) for dementia. The primary outcome is the difference in uptake between the two recruitment strategies. Secondary outcomes are change(s) in (1) the Lifestyle for Brain Health score, (2) individual health behaviours, (3) health beliefs and attitudes towards DRR and (4) compliance to the tailor-made lifestyle advice. Outcomes will be measured at 3, 6, 9 and 12 months after baseline. The effectiveness of this online tailor-made lifestyle programme will be evaluated by comparing Demin participants to a matched control group (lifelines cohort).

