
To our knowledge, none of the health behaviour intervention studies were aimed at a specific group of middle-aged adults with increased risk for dementia due to their parental family history of dementia. Therefore, this study aims to investigate the uptake and effectiveness of a tailor-made online lifestyle programme for dementia risk reduction (DRR) among middle-aged descendants of recently diagnosed (in the last 6 months) people with AD or VD in the Netherlands. This will give insight into what extent it is feasible to recruit middle-aged descendants of people with AD or VD at the memory clinics and whether these potential participants are willing to participate in a tailor-made online lifestyle programme in order to reduce their dementia risk.

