### Primary outcome

The primary outcome is the difference in uptake (eg, the percentage of eligible people that signed the online informed consent form and completed a risk assessment of the total number of eligible people) between the active and passive recruitment strategy. The total number of eligible people in each recruitment group (active vs passive) are based on the number of new cases of AD or VD in all memory clinics during the recruitment period, assuming an average of one child per patient with dementia receiving the envelope with the PIF including a login access number. Due to privacy regulations, it is not possible to collect data regarding the reasons for non-participation.

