BMI, body mass index; DBP, diastolic blood pressure; HbA1c, haemoglobin A1C; HDL, high-density lipoproteins; LDL, low-density lipoproteins; LIBRA, lifestyle for brain health; MIND-diet, mediterranean-DASH diet intervention for neurodegenerative delay; SBP, systolic blood pressure; SQUASH, short questionnaire to assess health-enhancing physical activity; TC, total cholesterol.

(2) The change in the individual health behaviours, including physical activity (minutes of moderate to vigorous physical activity per week), diet (mediterranean-DASH diet intervention for neurodegenerative delay score; 0–14), alcohol consumption (number of glasses of alcohol per week), smoking behaviour (current smoker (yes/no) and number of cigarettes/cigars a day), cognitive activity (leisure-time cognitive activity score and number of hours paid work), loneliness (overall loneliness score; 0–6) and social activity (number of contacts per 2 weeks) and their stage of change over time. The stages of change are categorised into pre-contemplation (1), contemplation (2), preparation (3), action (4) and maintenance (5).^33^

(3) Changes in beliefs and attitudes with regard to DRR are measured using the Motivation to Change Lifestyle and Health Behaviour for DRR Scale (MCLHB-DRR scale).^61 62^ The MCLHB-DRR scale is based on the HBM,^32^ which explains health-related behaviours. Seven subscales of the HBM were included: perceived susceptibility, perceived severity, perceived benefits, perceives barriers, cues to action, general health motivation and self-efficacy. Participants are asked to rate all items on a 5-point Likert scale, ranging from strongly disagree (score=1) to strongly agree (score=5). A higher score on each subscale reflects a higher motivation to change their lifestyle and health behaviour for DRR. The Dutch version of the MCLHB-DRR scale, consisting of 23 items, has shown to be valid in the Dutch general population aged between 30 and 80 years old.^63^

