### Statistical analyses

First, descriptive characteristics will be explored. The difference in uptake between the two recruitment strategies will be examined using multilevel logistic regression analyses in order to correct for clustering at memory clinic level. We will calculate the percentage with the corresponding 95% CI and use an alpha of 0.05 to test statistical significance.

The effectiveness of the online tailor-made lifestyle programme for DRR will be determined by, first comparing the change in LIBRA score, the individual risk factors and the MCLHB-DRR score between the active and passive recruitment strategy, and second comparing participants of the Demin study (active and passive recruitment strategy) to a control group consisting of Lifelines participants (large population-based cohort study (n>167 000)) (www.lifelines.nl)^64^ in outcome. Lifelines participants (age 40–60 years) with a parent with dementia will be matched (using propensity scores) on non-modifiable risk factors (age, gender and education) for dementia to participants of the Demin. Subsequently, multilevel analyses will be performed to examine the change in the LIBRA score and the individual health behaviours over time. In addition, possible confounding and interaction effects will be identified and corrected for in the analysis (eg, health literacy). We will calculate relative risks with 95% CIs and use an alpha of 0.05 to test significance.

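### Programme effectiveness is to be determined from an unranked set of secondary outcomes in two comparisons, with no deciding contrast, and the first comparison cannot show effectiveness

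*Protocol article*

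**What the plan says.** The Introduction gives the trial two aims: "this study aims to investigate the uptake and effectiveness of a tailor-made online lifestyle programme for dementia risk reduction". The abstract and the title say the same.

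Only the first aim has a primary outcome (Primary outcome section): "The primary outcome is the difference in uptake". The sample size calculation rests on that outcome alone.

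The second aim is handled in Statistical analyses, which opens: "The effectiveness of the online tailor-made lifestyle programme for DRR will be determined by, first comparing the change in LIBRA score". The outcomes of the first comparison are given as "first comparing the change in LIBRA score, the individual risk factors and the MCLHB-DRR score between the active and passive recruitment strategy". The second comparison sets all Demin participants against propensity-matched Lifelines participants and does not list its outcomes. Multilevel analyses of LIBRA and the individual health behaviours over time follow, and the paragraph ends with the significance rule: "We will calculate relative risks with 95% CIs and use an alpha of 0.05 to test significance".

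All of these outcomes are listed as secondary. LIBRA comes first among them, but no priority is stated. The second entry begins "The change in the individual health behaviours, including physical activity (minutes of moderate to vigorous physical activity per week" and goes on to diet, alcohol, smoking, cognitive activity, loneliness and social activity. The abstract adds four follow-up times: "Outcomes will be measured at 3, 6, 9 and 12 months after baseline".

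Study setting and design states that, once consent is signed, participants from both recruitment strategies go through the programme in the same way.

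**The concern.** A conclusion about one of the two title-level aims is to be drawn from many tests at 0.05, and the plan does not say which of them decides. Two things follow.

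First, the results can disagree. Physical activity might improve while LIBRA does not, or a difference at 3 months might be gone by 12. The plan then gives no answer to whether the programme was effective, and the choice would be made after the data are seen. Choosing among several tests each at 0.05 carries a false-positive risk above the nominal level.

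Second, the comparison listed first does not measure effectiveness. The two arms differ in how people were invited, not in what they received. A difference in LIBRA change between them would show that the two routes brought in people who respond differently. No difference would be equally compatible with a programme that works and one that does not. Reading either result as evidence on effectiveness would be a mistake, yet the text places this comparison among the ways effectiveness is determined.

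**Working it through.** **The plan's own figures.** The article states no overall error rate for effectiveness, so there is none to reproduce. Its sample size does reproduce for the cluster inflation: m = (15² + 25²)/(15 + 25) = 21.25; inflation = 1 + (21.25 − 1) × 0.05 = 2.0125; 188 × 2.0125 = 378. It uses uptake of 30% versus 50% only, so nothing below changes it.

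**Step 1: which tests can support a claim of effectiveness.** Both arms get the same programme, so active-versus-passive tests are set aside. The Lifelines comparison remains.

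**Step 2: how many Lifelines tests.** The article does not list them, so the count is an assumption. One test per outcome is counted, with no separate tests by time point and none for stages of change.
- LIBRA plus the seven behaviours named under Secondary outcomes: 1 + 7 = 8.
- LIBRA plus nine measures (smoking status and cigarettes per day counted separately, likewise cognitive activity score and paid hours): 1 + 9 = 10.
- LIBRA plus its 12 component factors: 1 + 12 = 13.

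**Step 3: error rate.** Each test is taken as two-sided at 0.05 (the article does not state sidedness), with critical value c = 1.96. All null hypotheses are taken as true and the matched comparison as free of bias. The k test statistics are standard normal with a common correlation ρ. The documents give no value for ρ, so the range 0 to 0.8 is shown.

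With ρ = 0:
- either direction: 1 − 0.95^k
- favourable direction only: 1 − 0.975^k

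For k = 8 these give 1 − 0.95⁸ = 33.7% and 1 − 0.975⁸ = 18.3%. For k = 13 they give 48.7% and 28.0%.

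With ρ > 0, condition on a shared standard normal term a and integrate over it:
- favourable: 1 − ∫ Φ((c − √ρ·a)/√(1−ρ))^k φ(a) da
- either direction: the same, with Φ((−c − √ρ·a)/√(1−ρ)) subtracted inside the bracket before raising to the power k

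| Tests | Direction | ρ = 0 | ρ = 0.3 | ρ = 0.5 | ρ = 0.8 |
|---|---|---|---|---|---|
| 1 | favourable | 2.5% | 2.5% | 2.5% | 2.5% |
| 8 | favourable | 18.3% | 15.2% | 12.5% | 7.9% |
| 10 | favourable | 22.4% | 17.8% | 14.4% | 8.6% |
| 13 | favourable | 28.0% | 21.4% | 16.7% | 9.6% |
| 1 | either | 5.0% | 5.0% | 5.0% | 5.0% |
| 8 | either | 33.7% | 30.0% | 25.0% | 15.8% |
| 10 | either | 40.1% | 35.1% | 28.7% | 17.3% |
| 13 | either | 48.7% | 41.8% | 33.4% | 19.2% |

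The chance of at least one false favourable result is therefore 7.9% to 28.0%. Dividing by 2.5% gives about 3 to 11 times the rate for a single named test.

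**The case against.** The strongest objection is that uptake is the only primary outcome, every effectiveness outcome is labelled secondary, and multiplicity rules for secondary outcomes usually sit in an analysis plan that is not shown. That is right as far as it goes: the trial's primary error rate is not inflated, and a missing adjustment is not the point made here. What remains is what the article itself fixes. It says effectiveness will be determined from this set, it ranks nothing in it, and it puts first a comparison that cannot show effectiveness.

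A second objection is that the article states no rule by which one significant result is enough. That also stands. The figures give the chance that at least one false result is available to be cited, not the chance that the investigators would cite it. Separate tests at each visit are likewise not stated; the multilevel analyses over time suggest joint modelling, so time points are left out of the count.

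A reader might go further and pool both comparisons, count 27 tests and put the chance of a false claim of effectiveness at about 48%. The documents do not support that. The text allows counts from about 17 to 35. The 48% requires an assumed correlation of 0.5 and counts results against the programme as well as for it; in the favourable direction alone, the same 27 tests give 24%. Most or about half of the 27, depending on how they are listed, are active-versus-passive tests, which say nothing about effectiveness.

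**Conclusion.** The point holds in limited form. The article ties a title-level aim to an unranked set of secondary outcomes in two comparisons, names no deciding contrast, and includes a comparison that cannot address the aim because both arms receive the same programme.

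On the Lifelines comparison alone, the chance of at least one false favourable result is about 8% to 28%, and about 13% to 17% at a correlation of 0.5, against 2.5% for one named two-sided test. In either direction it is about 16% to 49%, against 5%. The number of tests (8 to 13), the common correlation (0 to 0.8), two-sided testing and an unbiased matched comparison are assumptions, not figures from the article. The excess over a single named test is present at every combination tried. The part about active versus passive needs no arithmetic and does not depend on these assumptions.

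This should be corrected before the effectiveness data are analysed. It does not affect the uptake analysis.

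**What to change.** In Statistical analyses:

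1. State that the effectiveness claim rests on one contrast tested at two-sided 0.05: change in LIBRA from baseline, Demin participants versus matched Lifelines controls. Set the time at 12 months, the only Demin follow-up with physical examination and blood sample, or at the nearest time at which Lifelines supplies the LIBRA components. The article gives no Lifelines visit schedule, so this must be confirmed before the time is fixed.
2. Describe the active-versus-passive comparisons of change as showing differences by recruitment route, not as evidence of effectiveness.
3. Report the individual behaviours, MCLHB-DRR and other time points as supportive estimates with 95% CIs.

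The change is one of wording, apart from the check on what Lifelines can provide. The cost is that an isolated significant behaviour or subscale could no longer be claimed as evidence that the programme works. The target of 378 participants stays as it is.

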### Adverse events

The risk classification of this intervention is considered negligible, since only information and health advice is provided. Serious adverse events as a result of the intervention are not expected, thus no data safety and monitoring board is installed. Potential participants are informed about possible adverse events. For example, dementia risk assessment may help raising the awareness of their susceptibility in order to motivate health behaviour change,^32^ however, risk assessment could also have an unfavourable effect. Participants may become anxious about developing dementia and could experience more stress if they receive their health profile. Therefore, participants are clearly informed that the presence or absence of risk and protective factors is not a reassurance that they will develop dementia later in life. Furthermore, participants are informed that there is the possibility that unexpected medical findings can be found. In this case, participants receive a separate message in their personal inbox with the recommendation to contact their general practitioner to verify the results (hypertension, high cholesterol, renal dysfunction, diabetes) and discuss whether treatment is needed. Participants may consider online risk assessment as a privacy risk. In this study, all personal information is kept separately from the research data, and participants use a SMS-tan code to login in their personal account.

### Patient and public involvement

Descendants of people with dementia were involved in the development of the Demin website. We assessed the knowledge, beliefs and attitudes towards dementia and dementia risk reduction among descendants of people with dementia (focus group discussions). The results of the focus group discussions were used to develop the Demin website in order to improve the participant recruitment and encourage health behaviour change among participants.

### Ethics and dissemination

This study is approved by the Dutch Ministry of Health, Welfare and Sport according to the Dutch Population Screening Act. Research which is considered to be Population Screening on the ground of the Population Screening Act, for which ministerial approval is required, does not have to be assessed on the basis of the Medical Research Involving Human Subjects Act.^65^ Population screening is defined as ‘medical research in persons carried out on an entire population or a category thereof aimed at the detection of certain types of disease or certain risk indicators for the benefit of the participating subjects’.^66^ This project focuses on the attenuations of risk factors for dementia. Since these risk factors are merely lifestyle factors, a positive impact beyond dementia may be expected. Due to a healthy lifestyle more healthy life years are added to people’s lives, which may ultimately increase the risk on dementia as age is an important risk factor for dementia. This research is conducted in accordance to the international ethical guidelines.^67^

All participants give informed consent to participate in this study, by signing an electronic informed consort form using SMS-tan (see online supplemental file 3). Authorship will be allocated using the guidelines for authorship defined by the International Committees of Medical Journal Editors.^68^ The results of the trial will be submitted to an international peer-reviewed journal and presented at national and international conferences.

10.1136/bmjopen-2020-039439.supp3Supplementary data
